## Abstract

**Background:**

Two main therapies, pazopanib and sunitinib, are used in the first-line setting for metastatic renal cell carcinoma (mRCC). These two tyrosine kinase inhibitors (TKI) are equally effective in terms of survival; however, they frequently induce adverse events. In this setting, Health-Related Quality of life (HRQoL) is a key element in the choice between these two treatments and the evaluation of treatment effectiveness. It could be of interest to evaluate HRQoL in daily clinical practice to aid adequate therapy choice and management. Currently, the development of information and communication technology may allow HRQoL monitoring in routine practice. The objective of the QUANARIE study is to evaluate the use of HRQoL assessment in daily clinical practice for patients with mRCC treated with TKI using electronic patient-reported outcomes (e-PRO). The present article describes the key elements of the study protocol.

**Methods:**

The QUANARIE study is an interventional, prospective, multicentre trial. Patients diagnosed with mRCC initiating sunitinib or pazopanib treatment will be invited to complete the EORTC QLQ-C30 questionnaire, nine additional questions from the EORTC items library, and the EuroQoL EQ-5D, prior to each visit with the physician. Questionnaires will be completed by patients using tablets and/or computer terminals via the e-PRO software. The physician will have real-time access to a visual summary of the HRQoL evaluation. The primary objective is to assess the proportion of patients having good compliance with Routine Electronic Monitoring of HRQoL (REMOQOL) during the first 12 months. Physicians’ satisfaction with REMOQOL will be assessed as a secondary objective. We hypothesise that 80% of patients having good compliance with REMOQOL would be meaningful. A sample size of 56 patients would be needed.

**Discussion:**

The results of this study will show whether REMOQOL is feasible on a large scale and whether patients are receptive to this new practice. This study will also determine how real-time multidimensional evaluation of patient perception can help physicians in their daily practice and how they used it in conjunction with other clinical information to manage patient care.

**Trial registration:**

ClinicalTrials.gov; Identifier: NCT03062410; First Posted: February 23, 2017; Last Update Posted: August 9, 2017.

## Background

Two main therapies, pazopanib and sunitinib, are currently used in the first-line setting for advanced or metastatic renal cell carcinoma (mRCC) [1–3]. These two tyrosine kinase inhibitors (TKI) are equally effective in terms of survival; however, they frequently induce adverse events. In the Comparz trial, a randomised phase 3 trial, non-inferiority of pazopanib to sunitinib was shown [4]. From a safety perspective, half of the patients receiving these TKI require a dose modification, and approximately 20% discontinue due to adverse events. Health-Related Quality of Life (HRQoL) scores in the pazopanib group were better than those in the sunitinib group for fatigue and treatment side effects [4]. In this setting, HRQoL is a key element in the choice between the two treatments and the evaluation of treatment effectiveness. The PISCES study showed that HRQoL and safety were key influencing factors in patient and physician preference of pazopanib or sunitinib [5].

HRQoL can be defined as the patient’s subjective perception of the impact of their disease and its treatment(s) on their daily life; physical, psychological, and social functioning and well-being. HRQoL is measured using validated self-reported questionnaires such as the EORTC QLQ-C30 cancer-specific questionnaire.

HRQoL is part of the patient reported outcomes (PROs), which includes any outcome evaluated directly by the patient, and is based on the patient’s perception of a disease and its treatment(s) [6]. It includes HRQoL, anxiety, depression, and satisfaction with cancer care, among other factors.

HRQoL at treatment start has been demonstrated to be associated with overall survival (OS) following a cancer diagnosis [7, 8], especially in renal cancer [9]. Systematic reviews have highlighted that HRQoL provides additional prognostic information compared to conventional biomedical factors; thus, PROs may better reflect patient functioning and well-being. Patients may also have a perspective regarding their functioning that is more closely related to survival than clinician perspectives (including performance status and toxicities) [10]. Moreover, HRQoL may reflect biological parameters that are not covered by other prognostic factors [11]. A relationship may also exist between better HRQoL scores and positive health behaviours [12]. Consequently, interventions that aim to improve HRQoL scores may have a positive effect on survival.

Since HRQoL captures the patient’s subjective perception of the impact of their disease and treatment, monitoring HRQoL in daily clinical practice may help to personalise patient management.

Systematic reviews have reported that routine PRO monitoring in daily clinical care, used in conjunction with other clinical parameters, is associated with an improvement in symptom control and patient satisfaction with the care received [13, 14], in addition to increased use of supportive care measures [14]. A recent randomised phase III trial showed that routine monitoring of PRO, associated with the management of alert by nurses, improves HRQoL and OS [15, 16]. More specifically, routine monitoring of HRQoL enhances communication between physicians and patients, resulting in an improvement in HRQoL [15–18]. Routine monitoring of HRQoL in daily clinical care could help to adequately choose and manage therapy, and may be of added value in the evaluation of treatment tolerance [19], customisation of supportive care [20], and the adequate assessment of treatment benefit from the patient’s point of view.

Currently, physicians mainly use OS or RECIST progression-free survival (PFS) and toxicity evaluated by the National Cancer Institute Common Terminology Criteria for Adverse Events version 4.0 (NCI CTCAE V4) as a guide to the evaluation of treatment efficiency and tolerance. Even though HRQoL is frequently evaluated in randomised phase III trials [21], routine HRQoL monitoring in daily care has not become widely implemented in routine care delivery [22]. Measuring HRQoL in routine practice has long faced a logistic issue: HRQoL questionnaires are usually filled on paper forms, and the scores must be calculated before the results can be interpreted [23, 24]. Currently, PRO measures can be collected electronically as the so-called ePRO measures, on computers, tablets, or smartphones. For instance, the software company ESD (Evaluation Software Development), has been developing the CHES Platform (Computer-Based Health Evaluation System; https://ches.pro/index.php/ches), which is a specialised software dedicated to the assessment, storage, and processing of ePRO data. One of the functions of the CHES Platform is the implementation of Routine Electronic Monitoring of HRQoL (REMOQOL) in daily oncology practice using EORTC QLQ measures. Besides, a recent systematic review reported that the QLQ-C30 was the most frequently used questionnaire in randomised controlled trials (RCTs) evaluating the routine electronic monitoring of PRO [14]. Several experiments of routine electronic monitoring of PRO have been successfully conducted [15, 18, 25]; however, it remains to be explored whether REMOQOL can be used on a larger scale, especially in oncology centres that are not necessarily involved in PRO research, without “clinician champions” [22], and in the French context of cancer-patient care.

The objective of the QUANARIE study is to evaluate the use of REMOQOL in daily clinical care for patients with mRCC treated with TKI using electronic HRQoL questionnaires and real-time feedback to physicians on a multicentre scale. This article describes key elements of the study protocol.

## Methods/design

### Study design

The QUANARIE study is an interventional, prospective, single-arm and multicentre trial involving nine French oncology centres. These nine medical institutions are located in Eastern France and cover a wide panel of centres for cancer care: three establishments specialising in cancer care (French Comprehensive Cancer Centres), three private clinics, two university hospitals, and one community hospital. The number of patients with mRCC ranges from 5 to 10 to 50–70 annually, depending on the centre*.*

The QUANARIE study will be proposed to patients diagnosed with mRCC initiating TKI anti-vascular endothelial growth factor (VEGF) treatment (sunitinib or pazopanib). The choice of TKI treatment will be at the discretion of physician, and two cohorts of equal sample size will be set up. Thus, when the required sample size is reached in one of the two cohorts, recruitment will be ceased for that cohort. There will be no randomisation or comparison between the two groups.

Patients will be invited to complete the following questionnaires prior to each visit with the physician (Table 1):The EORTC QLQ-C30 cancer-specific questionnaire;Nine items from the EORTC Item Library, exploring six supplementary symptomatic dimensions frequently described in patients treated with TKI;The EuroQoL EQ-5D utility questionnaire [26].

**Table 1 Tab1:** Schedule of enrollment, interventions, and assessments (SPIRIT Flow Chart)

	STUDY PERIOD				
	Enrolment	First Visit	Subsequent Visit	End of Treatment	End of Study
		V1	Vx		
Informed consent	x				
Inclusion/exclusion criteria	x				
Cohort allocation (sunitinib/pazopanib group)	x				
Socio-demographic data	x				
Renal cell carcinoma history	x				
Prior medication review	x				
CHES software training	x				
Delivery of passwords, username and leaflet	x				
Level of experience with computer tools	x				
Full physical examination	x	x	x	x	
Karnofsky index	x	x	x	x	
Adverse events monitoring (NCI CTCAE V4)	x	x	x	x	
TKI prescription/dose adaptation	x	x	x	x	
Concomitant medications	x	x	x	x	
Supportive care prescription		x	x	x	
Electronic questionnaire EORTC QLQ-C30 + 9 items EORTC Library Item		x	x	x	
Electronic questionnaire EuroQoL EQ-5D-5L		x	x	x	
Need help to fill out questionnaires		x	x	x	
Location (home or hospital) where the patient completes the questionnaire		x	x	x	
Measure of time to fill the questionnaires		x	x	x	
Progression and subsequent anti-cancer treatment if applicable			x	x	x
Survival status		x	x	x	x
Satisfaction physician questionnaire					x
Satisfaction research assistant questionnaire					x

The QLQ-C30 includes 30 items and measures five functional scales (physical, role, emotional, cognitive, and social functioning), global health status (GHS), financial difficulties, and eight symptom scales (fatigue, nausea and vomiting, pain, dyspnoea, insomnia, appetite loss, constipation and diarrhoea). These scores vary from 0 (worst) to 100 (best) for the functional dimensions and GHS, and from 0 (best) to 100 (worst) for the symptom dimensions. Six supplementary dimensions: epigastralgia, mouth pain, skin toxicity, hair loss, taste changes, and bone pain, will be explored through nine items from the EORTC Item Library (http://www.eortc.be/itemlibrary/#). These items were chosen to assess the most frequent adverse events related to sunitinib and pazopanib that are not covered in the core EORTC QLC-C30 questionnaire [27].

Patients will fill out the electronic questionnaires using tablets and/or computer terminals via the CHES software) on the day of their physician visit in the waiting room or at home via a secured portal 24–48 h before.

The physician will have real-time access to a visual summary of the HRQoL evaluation (Fig. 1), which will provide the possibility of using HRQoL data during the visit to adapt the management of TKI and supportive care.

**Fig. 1 Fig1:**
[figure not shown]
ePRO with the CHES software. Questionnaires are completed by patients using tablets and/or computer terminals via the CHES software (Computer-Based Health Evaluation System; https://ches.pro/index.php/ches) prior to each consultation at the oncology centre (waiting room) or at home via a secured portal. The physician will have real-time access to a visual summary of the HRQOL evaluation

The frequencies of follow-up visits and medical exams are not pre-specified and will be as in daily clinical practice for patients treated with sunitinib or pazopanib. Investigators will have to refer to the Summary of Product Characteristics (SmPC) for the marketing authorisations of sunitinib and pazopanib for follow-up of patients and forbidden drugs.

The inclusion period is expected to last 12 months, and the follow-up duration will be two years. Final analysis of the primary objective will take place after 12 months, for a total study duration of 36 months (12 months + a 24-month follow-up).

### Description of materials

The CHES software is a service for ePRO questionnaire administration, storage of ePRO data, and immediate graphical presentation of ePRO results. Patients will be asked to complete questionnaires at each physician visit, from TKI initiation to the end of treatment. This software was developed by the academic spin-off company, ESD and is supported by the EORTC Quality of Life Group, with the aim of creating a software tool available for HRQoL studies and daily clinical practice [28].

### Characteristics of participants

#### Key eligibility criteria are the following

Presence of histologically or cytologically confirmed renal carcinoma that is locally advanced, nonresectable, or metastatic, and initiation of an oral TKI anti-VEGF treatment (pazopanib or sunitinib);Estimated life expectancy greater than 3 months;Able to understand French and complete study questionnaires;Aged 18 years or older;Signed an informed consent form.

#### Key exclusion criteria are the following

Prior systemic treatment for metastatic renal cancer other than immunotherapy. Pretreatment or concomitant treatment with biphosphonate or denosumab is allowed;Any acute or chronic disease (e.g., severe COPD) that may affect the patient’s ability to receive the treatment under study or that may render the interpretation of toxicities or adverse events difficult;HIV positive;History of active chronic hepatitis, including subjects who are carriers of the hepatitis B or C viruses;History of digestive pathology that could compromise the absorption of an oral TKI.

#### Key trial objectives

The primary objective of the QUANARIE study is to evaluate the proportion of patients having good compliance with REMOQOL during the first 12 months of treatment.

The key secondary objectives are the following:To report the number of patients to whom the study was proposed divided by the number of patients initiating sunitinib or pazopanib treatment in each centre;To report the number of patients who agreed to participate in this study as compared with the number of refusals divided by the total number, by centre and by molecule type (sunitinib or pazopanib);To estimate the rate of missing data defined as the numbers of completely or partially filled items by HRQoL questionnaire and for each measurement time. We will consider a questionnaire as filled out if at least 10 items are completed;To Describe the toxicities collected by the physician according to the NCI CTCAE V4 and reported by the patient according to the eight symptomatic dimensions of the QLC-C30 questionnaire and the six supplementary symptomatic dimensions;To evaluate Physicians’ satisfaction regarding the CHES software and REMOQOL by a questionnaire submitted at the end of the inclusion.

The exploratory objectives are the following:To estimate OS, defined as the time from the start of treatment to death;To estimate PFS, defined as the time from the start of treatment to progression or death;To estimate Time to deterioration of HRQoL (TTD): TTD will be defined as the time from the start of treatment to the first significant deterioration (either increase or decrease depending of the scale) in a HRQoL score as compared with the baseline score with no further significant improvement as compared to the baseline score, or death [29, 30]. Pre-specified targeted HRQoL dimensions will be global quality of life (QL), physical functioning (PF), and fatigue (FA). In these dimensions, will be considered as significant a deterioration over time of ten points at least and an improvement of eight points in QL, seven points in PF and nine points in FA [31].

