## Abbreviations

CHES: Computer-Based Health Evaluation System software
COPD: chronic obstructive pulmonary disease
EORTC: European Organisation of Research and Treatment of Cancer
ePRO: electronic patient-reported outcome
EQ-5D: European Quality of Life – 5 Dimensions Questionnaire
ESD: Evaluation Software Development
FA: Fatigue
FDA: US Food and Drug Administration
HRQoL: Health-Related Quality of Life
ORR: Overall response rate
OS: Overall survival
PF: Physical Functioning
PFS: Progression-free survival
PRO: Patient-reported outcome
QL: Global Quality of Life
QLQ-C30: Quality of Life Core Questionnaire
RCC: Renal cell carcinoma
REMOQOL: Routine Electronic Monitoring of HRQoL
SmPC: Summary of product characteristics
TKI: Tyrosine kinase inhibitors
TTD: Time to HRQoL deterioration
TTP: Time to progression
VEGF: Vascular endothelial growth factor

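### A single 10-item threshold cannot be met by the EQ-5D and passes a QLQ-C30 that is two-thirds empty, and the missing-data rate is defined by counting what is filled

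*Protocol article*

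**What the plan says.** The secondary objectives (Key trial objectives) include estimating "the rate of missing data defined as the numbers of completely or partially filled items by HRQoL questionnaire", at each measurement time. The next sentence sets the completeness rule: "We will consider a questionnaire as filled out if at least 10 items are completed". The article gives no other threshold for any instrument.

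The instruments differ in length. Under Study design, "The QLQ-C30 includes 30 items", and six further symptom dimensions "will be explored through nine items from the EORTC Item Library". The abbreviation list expands EQ-5D as a "5 Dimensions Questionnaire"; the number of items is not given.

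The article is not consistent on what one questionnaire is:

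- Study design says "Patients will be invited to complete the following questionnaires prior to each visit with the physician" and then lists three entries: the QLQ-C30, "Nine items from the EORTC Item Library, exploring six supplementary symptomatic dimensions", and the EQ-5D.
- Table 1 puts the QLQ-C30 and the nine items in one row and the EQ-5D-5L in another.
- Follow-up assessments names only the QLQ-C30 and the EQ-5D.
- The Discussion describes the extra items as added to the QLQ-C30.

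The term *filled out* returns in Primary outcome definition (the 66% compliance criterion) and in Population analysis (at least one filled-out questionnaire is needed to be evaluable). Neither section defines it.

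**The concern.** An absolute count works only if every instrument is long enough to reach it and if reaching it means something similar for each. Here one instrument is shorter than the threshold. For the longest one the threshold is a third of its items, so a form with most answers absent is recorded as filled out.

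The missing-data objective has a separate defect: it names a rate of missing data but defines it as a number of items present. An analyst who followed the text would report a figure that rises as completion improves.

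At stake are the completion and missing-data results, which are central to a feasibility study. If the rule carries over to the primary outcome, the unit in which compliance is counted is affected too.

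**Working it through.** **The plan's own figures.** The article gives no derivation for the 10-item threshold, so there is none to reproduce. The downstream decision rule does reproduce. With exact binomial probabilities for 45 evaluable patients and success at 33 or more, P(X ≥ 33 | 60%) = 0.0446 and P(X ≥ 33 | 80%) = 0.9005. Hence β = 1 − 0.9005 = 0.0995, against the stated 9.9%. The sample size is not in dispute here.

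**Inputs.** Threshold: 10 items (Key trial objectives). QLQ-C30: 30 items; supplementary set: 9 items (Study design). EQ-5D: five dimensions (Abbreviations). I assume one item per dimension, giving 5, or 6 if an overall rating is added.

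**Step 1: can the threshold be reached, and how much may be empty?** The share needed is 10 / m, where m is the number of items; the share that may be empty is 1 − 10 / m.

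| Unit taken as a questionnaire | m | Share needed | May be empty |
|---|---|---|---|
| QLQ-C30 alone | 30 | 10/30 = 33.3% | 66.7% |
| QLQ-C30 + nine items (Table 1) | 39 | 10/39 = 25.6% | 74.4% |
| Nine items alone (Study design list) | 9 | cannot be reached (9 < 10) | – |
| EQ-5D alone | 5 to 6 | cannot be reached (6 < 10) | – |

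The EQ-5D result is the same wherever the article lists the instruments, because the EQ-5D always stands apart. The result for the nine items depends on whether the Study design list or Table 1 governs.

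**Step 2: what can ten QLQ-C30 answers leave out?** Study design gives 5 functional scales + 1 global health status + 1 financial difficulties + 8 symptom scales = 15 scales. If each item feeds one scale, ten answers touch at most ten scales, so at least 15 − 10 = 5 are blank. The targeted dimensions are three of the 15. The other 15 − 3 = 12 scales hold at least one item each, so at least 12 items lie outside the targets. Since 12 ≥ 10, all ten answers can fall outside global quality of life, physical functioning and fatigue. The form then counts as filled out with no data for any targeted score.

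**Step 3: the missing-data rate.** For one QLQ-C30, compare the text read literally with the usual definition:

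| Items answered | As defined (filled items) | (due − completed) / due |
|---|---|---|
| 30 | 30 | 0/30 = 0% |
| 10 | 10 | 20/30 = 66.7% |
| 0 | 0 | 30/30 = 100% |

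The literal quantity moves in the wrong direction and is a count, not a rate.

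**Step 4: does it reach the primary outcome?** Key trial objectives holds the only definition of *filled out*. Primary outcome definition and Population analysis use the term without another one. The natural reading is that they inherit the 10-item rule, but the rule is written under a secondary objective and neither section refers to it.

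**The case against.** The strongest reply is that this is a feasibility study of engagement with monitoring, not of whether scores can be computed. A permissive threshold fixed in advance is then a legitimate choice, and details by instrument may sit in a full protocol or analysis plan that is not shown. The article also gives no rate of partial completion and does not say whether the software lets patients skip items, so the nearly empty form may be rare. The inverted wording looks like a slip: filled and missing are complements once the number due is known, and Analysis of secondary endpoints speaks plainly of reporting the rate of missing data.

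Much of this stands. It limits the consequences and argues against making computable scores the primary unit of compliance, since the 60% and 80% hypotheses were set without that requirement. It does not rescue the rule. The article states a threshold that one of its own questionnaires cannot meet, which is different from leaving a detail to another document. Nor does the plain phrase in the analysis section replace the definition given under the objectives.

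Three stronger readings are tempting but not supported:

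- *The nine items can never pass.* This holds only if they are a separate questionnaire. Table 1, Follow-up assessments and the Discussion all point to their being part of an extended QLQ-C30.
- *Two of the three instruments would show 100% missing data.* The missing-data rate is defined on items, so an answered EQ-5D item still counts. It is the filled-out classification that the EQ-5D cannot meet.
- *Ten of 44 items is enough (30 + 9 + 5).* Pooling the whole battery conflicts with the wording that applies the measure by questionnaire, and it cannot be combined with the claim that single instruments fail.

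**Conclusion.** The rule is wrong as written in two respects. First, one absolute count does not suit instruments of different length. The EQ-5D (5 to 6 items, an assumption from its five dimensions) cannot be classed as filled out, while a QLQ-C30 qualifies with 20 of 30 items empty and possibly nothing for the three targeted scores. Depending on how the nine items are treated, either they too cannot qualify or the combined form qualifies on 26% of its items. Second, the missing-data rate is defined as its opposite, with no denominator.

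A reader might go on to infer that the primary compliance proportion is inflated. The document does not show that. The link rests on a shared term, the frequency of near-empty forms is unknown, and no effect on the 33-of-45 rule can be computed. The sample size is unaffected. The point deserves correction before analysis, but it does not show that the primary result would change.

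**What to change.** 1. Replace the single count with a proportion-based or instrument-specific rule. One workable option is at least half the items: 15 of 30 for the QLQ-C30, or 20 of 39 for the combined set (39/2 = 19.5, rounded up), with a separate rule for the EQ-5D. State whether the nine items are their own questionnaire or part of the QLQ-C30.
2. Define the missing-data rate as (items or questionnaires due − completed) / due, per instrument and visit.
3. State which completion rule governs Primary outcome definition and Population analysis.
4. Add a sensitivity analysis of primary compliance in which a visit counts only if global quality of life, physical functioning and fatigue can all be computed.

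The cost is a wording change and minor programming. Reported completion may be lower under the stricter rule. Because item 3 settles the unit of the primary endpoint, it should be decided before the compliance data are examined.
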